### Sample size {14}

Sample size calculation is based on the average comparison of crossover tests: the *t*-test for difference of means in 2 × 2 crossover design (N-Query software). We assume that the use of the rigid obturator will be associated with a mean VHI score of 34 and a standard deviation of 15 [14, 15]. To ensure a power of 90%, an alpha risk of 5%, and an expected difference of 15 points between the reference and new obturator, 7 patients per treatment sequence are required, thus 14 in all. No drop-out was included in the sample size calculation due to the small duration of the study follow-up (3 months).

### Recruitment {15}

For achieving adequate participant enrolment to reach the target sample size, all new patients meeting eligibility criteria will be given the opportunity to participate in the study. A close coordination is made between the Dental departments and the Oncology and Maxilla-facial surgery departments of both teaching hospitals to identify and refer adequately potential participants.

## Assignment of interventions: allocation

### Sequence generation {16a}

Assignments will be prepared by the statistician of the Bordeaux University Hospital Clinical Trial Unit (CTU) prior to trial commencement, using SAS ver. 9.4 software (SAS Institute Inc., Cary, NC, USA). Randomization is balanced (1:1 ratio) in random permuted blocks and stratified on the site.

### Concealment mechanism {16b}

The secure CTU website will contain data on patient eligibility, allocation numbers, and randomization group. The CTU statistician and computer scientist are the only ones with access to the randomization list.

### Implementation {16c}

The randomization list is implemented in the RedCap software by the study statistician. Access to the randomization list via the e-CRF is limited to the study investigators.

## Assignment of interventions: blinding

### Who will be blinded {17a}

N/A. Neither investigator nor patient will be blinded.

### Procedure for unblinding if needed {17b}

N/A. Not applicable.

## Data collection and management

### Plans for assessment and collection of outcomes {18a}

The VHI questionnaire will be administered by the investigator at baseline and 1 month after the delivery of either prosthesis. The secondary outcomes will be obtained from self-administered questionnaires completed at baseline and 1 month after each device is tested. Patient’s answers will be entered in e-CRF through a dedicated REDCap entry mask.

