### Outcomes {12}

The primary outcome will be phonation-related disability based on the overall score of the Voice Handicap Index (VHI) [14, 15] at 1 month after delivery of either prosthesis. This ranges from 0 and 120; the VHI includes 30 items exploring functional, emotional, and physical domains. The secondary outcomes include the Deglutition Handicap Index (DHI, 30 items, maximum score 120) and the EORTC QLQ-C30 (a general questionnaire containing the QLQ-H&N35 modules [35 items in all] exploring the health-related quality of life) prepared by the European Organization for Research and Treatment of Cancer (EORTC) [16–18]. Both questionnaires are scored from 0 to 100 and will be evaluated at 1 month after the delivery of either prosthesis. All questionnaires have been translated into French and validated.

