## Oversight and monitoring

### Composition of the coordinating center and trial steering committee {5d}

The steering committee is made up of the following people: [name] [name] (chairman, principal investigator), [name] [name] (clinical investigator and responsible for the obturator manufacturing), [name] [name] (clinical investigator and responsible for the center of Toulouse), [name] [name] (methodologist), a statistician, [name] [name] (pharmacist), and a representative of the sponsor. This committee checks ethics. With the Center for Methodology and Data Management, this committee checks also the status of the research, possible problems, and available results. It decides on any relevant modification of the protocol necessary for the continuation of the research. It may propose to extend or interrupt the research.

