## Discussion

Our hypothesis is that the new membrane obturator will improve speech more than the standard obturator [19]. The primary outcome is therefore the Voice Handicap Index (VHI) score. This dysphonia self-assessment scale quantifies the extent to which a phonation disorder compromises the quality of life and assesses the psychosocial consequences. The French version has been validated and used in patients with oropharyngeal cancer [14, 20]. The Deglutition Handicap Index (DHI) is a derivative of the VHI that focuses on swallowing [18]. This questionnaire quantifies the adverse effects of swallowing disorders and the score will serve as a secondary outcome.

Soft palate defects arise in various ways. However, we will include only patients who have undergone surgical tumor removal. Soft palate trauma is very rare. Patients with congenital defects such as palatal clefts usually develop mechanisms that compensate for speech and swallowing difficulties; these become entrenched and are difficult to bypass. Oncology patients should be able to adapt to the use of a new device; our new prosthesis should restore speech and improve swallowing, improving the quality of life [19].

“Quality of life” includes physical components (autonomy and physical activities), psychological components (anxiety, depression, and emotion), relational components (family, social, and professional), symptomatic components (repercussions of the disease and treatment thereof), and other components (sexuality and self-image). The relevant psychometric tools (scales or questionnaires) are easy to use and well standardized. The QLQ-H&N35/EORTC QLQ-C30 questionnaires of the EORTC are commonly used for ear-nose-and-throat assessments [16, 17, 21, 22]. French versions have been employed to evaluate patients with oropharyngeal cancers [21, 23, 24]. Both questionnaires yield several scores (thus not single overall scores) and therefore cannot serve as principal assessment criteria. In addition, they explore aspects of the quality of life that are not related to our intervention. We will perform secondary analyses only.

The crossover design is optimal for several reasons:

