The two prostheses are removable and their effects do not persist. Thus, the initial state is re-attained at the beginning of the second period; no “washout” is requiredThere is no further substance loss over the test periodThe risk of loss to follow-up is minimal; the test periods are short (1 month)Outcomes of interest will be measured at 1-month intervals; no conditioning effect is in play

This study will yield high-quality evidence on the utility of a new device that should greatly improve the management and the quality of life of patients with acquired velar insufficiencies. Such insufficiencies cause malnutrition, reduce the quality of life, can lead to patient refusal to accept care, and may trigger psychological and social isolation associated with poor communication and societal integration [8, 25]. Often, the rigid obturator does not restore oronasal partitioning; the patient remains disabled. The membrane obturator will remedy swallowing and phonation deficiencies more effectively and rapidly than a rigid obturator.

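### The unblinded investigator administers the VHI, the primary outcome, while the secondary questionnaires are self-completed; any interviewer effect that differs by device would bias the primary comparison

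*Protocol article*

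**What the plan says.** All references are to the protocol article.

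- **Outcomes {12}** fixes the primary endpoint: "The primary outcome will be phonation-related disability based on the overall score of the Voice Handicap Index (VHI"). The score has 30 items, runs from 0 to 120 and is taken 1 month after delivery of each prosthesis.
- **Plans for assessment and collection of outcomes {18a}** sets the mode for the primary outcome: "The VHI questionnaire will be administered by the investigator at baseline and 1 month after the delivery of either prosthesis". The next sentence sets a different mode for the rest: "The secondary outcomes will be obtained from self-administered questionnaires completed at baseline and 1 month after each device is tested".
- **Discussion** describes the VHI as follows: "This dysphonia self-assessment scale quantifies the extent to which a phonation disorder compromises the quality of life and assesses the psychosocial consequences".
- **Who will be blinded {17a}**: "Neither investigator nor patient will be blinded".
- **Discussion** also states the expected result: "The membrane obturator will remedy swallowing and phonation deficiencies more effectively and rapidly than a rigid obturator".

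The article gives no reason for the two modes and describes no safeguard, such as an interviewer who is independent of treatment.

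**The concern.** The result that decides the trial is collected in the mode more open to outside influence, and the supporting results in the less open one. The VHI asks for the patient's own view of a voice handicap. If an investigator who knows the device puts the questions, the answers can be affected by how items are put or explained, or by the patient's wish to please. The article openly expects the membrane obturator to do better, so an influence that differs between the two devices is plausible.

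What is at stake is the primary treatment difference. An effect that follows the device has the same form in the data as a treatment effect, so no later analysis can separate the two.

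**Working it through.** **1. Which interviewer effects matter.** Write the VHI score of patient *i* in period *j* on device *d* as patient effect + period effect + treatment effect of *d* + interviewer effect *b(d)*. The treatment contrast compares the two devices within patients, so it estimates

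(true treatment difference) + [*b*(membrane) − *b*(rigid)].

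- If *b*(membrane) = *b*(rigid), the bracket is zero. A general tendency to report less handicap face to face therefore drops out.
- If the two differ, the bracket stays in full. The period term does not absorb it, because each device is used in both periods across the two sequences. The random patient effect does not absorb it, because it varies within the patient.

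**2. The plan's own figure.** Inputs from Sample size {14}: difference 15, SD 15, alpha 5% (sidedness not stated; two-sided assumed), power 90%, 7 per sequence, 14 in all, no drop-out. For the 2 × 2 crossover *t*-test, SE = SD of differences / √N, df = N − 2, and power comes from the noncentral *t* distribution.

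- With 15 read as the SD of within-patient differences: SE = 15/√14 = 4.01, df = 12, noncentrality = 15/4.01 = 3.74, power 92.9%. The smallest balanced N reaching 90% is 14, so the stated sample size is reproduced.
- With 15 read as a single-score SD and zero within-patient correlation: SD of differences = 15√2 = 21.2, SE = 21.2/√14 = 5.67, power at N = 14 is 68%.

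The section gives 15 as the SD of the score with the rigid obturator, so both readings are carried forward. How the VHI is administered does not enter this calculation, and the sample size is not in question here.

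**3. Illustrative size.** The documents give no figure for interviewer bias, so the shifts below are assumptions. With no true difference, the two-sided rejection rate at N = 14 is the noncentral *t* tail probability beyond ±2.179 on 12 df, with noncentrality = shift/SE.

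| Device-dependent shift | Per item (÷ 30) | Share of the 15-point difference | Rejection rate, SD of differences 15 (SE 4.01) | Rejection rate, SD of differences 21.2 (SE 5.67) |
|---|---|---|---|---|
| 0 | 0 | 0% | 5% | 5% |
| 2 points | 0.07 | 13% | 7.5% | 6.2% |
| 4 points | 0.13 | 27% | 15.1% | 10.0% |
| 6 points | 0.20 | 40% | 28.1% | 16.4% |

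**4. Whether it is avoidable.** The DHI and EORTC forms are already self-completed at baseline and after each device {18a}. The timeline (Table 1) shows a single row of questionnaire surveys at the same visits. Eligibility criteria {10} require the ability to read French. Self-completion of the VHI therefore needs nothing that the trial does not already have.

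**The case against.** **Administering may only mean handing out.** The same section goes on to speak of the patient's answers being entered in the e-CRF, and a fuller protocol could hold detailed instructions. This stands in part: the article does not settle the point. But the next sentence uses the contrasting term for the other questionnaires, which favours the interview reading. If handing out was meant, the sentence should say so.

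**Who conducts it.** The steering committee {5d} lists a person described as "clinical investigator and responsible for the obturator manufacturing". A reader might infer that the patient answers to the person who made or fitted the device. The documents do not support that: they do not say which investigator administers the VHI or who fits the prostheses, and there are two centres. What the documents do support is that investigators are unblinded.

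**Any interviewer effect biases the trial.** A reader might infer this too. It is not so, because an effect common to both devices cancels (step 1 of the working).

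**The patient is unblinded anyway.** This is correct. The patient is the rater and knows the device, so expectation bias remains after the change, and nothing shows that the interviewer part is the larger one. That limits the benefit, but it is no reason to keep a second source of bias that can be removed.

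**The magnitudes are assumed.** This is also correct. A 6-point shift is not small, since it is 40% of the target difference, and the rates depend on how the SD is read. Hence both columns are shown, as illustration only.

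**Conclusion.** The point holds. The article fixes a mode of collection for the primary outcome that is more exposed to influence than the mode used for the secondary outcomes, without stating a reason or a safeguard. This is a choice that the document makes and not a detail left to another document.

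The bias arises only to the extent that the interviewer effect differs between devices. Lack of blinding makes that possible; the documents do not show that it occurs, or how large it would be. The illustrative error rates assume N = 14, a two-sided 5% test, no true difference and an SD of within-patient differences of either 15 or 21.2.

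A reader might conclude that the defect invalidates the primary result and must be fixed before the trial can be relied on. That goes too far: the sample size and the analysis model are untouched, the effect is unquantified, and the remedy removes only the interviewer's share of an open-label bias. It should be fixed, as a cheap improvement.

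**What to change.** Amend Plans for assessment and collection of outcomes {18a} so that the patient completes the VHI alone at baseline and after each device, in the same session and manner as the DHI and EORTC questionnaires, and before discussing the device with the investigator. Staff check only that the form is complete and enter it in REDCap.

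Costs and limits:

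- The change needs one sentence in the protocol and an instruction to both sites, with no extra visits.
- Some items may be skipped; the completeness check limits this.
- Recruitment began in July 2020 (Trial status). The change may therefore count as an important amendment, which under section {25} needs a favourable ethics committee opinion and ANSM authorisation before it is implemented.
- Changing partway would mix two modes among 14 patients. For those already enrolled, record the mode used and keep it the same in both periods, so that each within-patient comparison is made under one mode.
- The patient's own expectation bias remains and should be acknowledged when the result is interpreted.

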### Plans to promote participant retention and complete follow-up {18b}

A patient will be considered as lost-to-follow-up if no contact can be made during 3 months, after an active search from the investigator. Participants will receive no financial compensation but they will be given both obturators at the end of the study.

### Data management {19}

Data are entered anonymously in e-CRF through a dedicated REDCap entry mask. Data collection will be monitored by a clinical research assistant. When requested, the investigator will clarify data. Data management is under the responsibility of the Bordeaux University Hospital CTU.

### Confidentiality {27}

The final trial dataset will be available to the clinical research assistants, data managers, and statisticians, subject to professional secrecy. Data are anonymous.

### Plans for collection, laboratory evaluation, and storage of biological specimens for genetic or molecular analysis in this trial/future use {33}

N/A. No collection.

## Statistical methods

### Statistical methods for primary and secondary outcomes {20a}

Scores will be evaluated in terms of mean, standard deviation, median, range, and first and third quartiles. To assess the results, a mixed-effects linear regression model will be used to analyze effects of “treatment” and “period.” Analyses will vary by whether an interaction between treatment and period is or is not apparent. The response variable of the linear regression model will be the overall VHI score; the explanatory variables will be the treatment group (a fixed effect), the administration period (a fixed effect), the interaction between treatment and period (a fixed effect), and the patient (a random effect). The same statistical methods will be used for the secondary outcomes.

Sensitivity analyses will be performed by adding “interaction treatment*period.”

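### The protocol does not fix the primary treatment effect: the analysis may change with an observed treatment-by-period interaction, and that term is placed both in the main model and in a sensitivity analysis

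*Protocol article*

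**What the plan says.** Three statements in the protocol article's section on statistical methods (item 20a) bear on the point.

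- The choice of analysis depends on the data: "Analyses will vary by whether an interaction between treatment and period is or is not apparent".
- The mixed model for the overall VHI score has treatment, period and a random patient effect, and its list of explanatory variables also contains "the interaction between treatment and period (a fixed effect").
- The section closes with "Sensitivity analyses will be performed by adding", followed by that same treatment-by-period term.

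The section applies the same methods to the secondary outcomes.

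Two other sections matter. The sample size section (item 14) sizes the trial on a t-test for a 2×2 crossover, that is, on a within-patient comparison, and concludes that "7 patients per treatment sequence are required, thus 14 in all". The Discussion defends the crossover design without washout on the ground that "The two prostheses are removable and their effects do not persist".

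**The concern.** A term that is already in the primary model cannot be added to it in a sensitivity analysis. One of the two statements must be wrong, and the text does not say which. The branching sentence then lets the observed data choose between analyses.

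This matters more in a 2×2 crossover than in most designs. With two sequences and two periods, treatment-by-period is the same contrast as sequence, and it cannot be separated from differential carry-over. It is estimated from patient totals, 7 patients against 7, so it is imprecise. It is also correlated with the period-1 comparison that is conventionally used after a positive test. Selecting the analysis by such a pre-test can raise the false-positive rate of the whole procedure, and it can replace the within-patient contrast on which the trial was sized with a between-patient one.

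**Working it through.** **Inputs.** Sample size section: "To ensure a power of 90%, an alpha risk of 5%, and an expected difference of 15 points between the reference and new obturator"; "a mean VHI score of 34 and a standard deviation of 15"; 7 patients per sequence. Assumptions not in the article: a two-sided test; equal variances in both periods; a pre-test of the interaction at 5% or 10%; within-patient correlation ρ from 0 to 0.8; and, for the two-stage calculation, period 1 alone after a positive pre-test.

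**1. The plan's own figure.** The SD of within-patient differences is 15·√(2(1−ρ)), which is 15 at ρ = 0.5. The treatment estimate then has SE = 15/√14 = 4.01 and noncentrality 15/4.01 = 3.74 on 12 df. Power is 92.9% with 7 per sequence and 87.6% with 6. So 7 per sequence is reproduced, and ρ = 0.5 is the natural central case.

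**2. The period-1 contrast.** SE = 15·√(2/7) = 8.02, noncentrality 15/8.02 = 1.87 on 12 df, power 40.6%.

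**3. The pre-test.** A patient total has SD 15·√(2(1+ρ)) = 25.98 at ρ = 0.5. The between-sequence difference in totals has SE 25.98·√(2/7) = 13.89. For a carry-over difference of 15 points, as large as the whole target effect, noncentrality is 15/13.89 = 1.08. Power is 16.9% at the 5% level and 27.0% at the 10% level. The correlation between this contrast and the period-1 contrast is √((1+ρ)/2) = 0.87 at ρ = 0.5.

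**4. The two-stage rule, if period 1 alone follows a positive pre-test.** Simulation with 200,000 trials per setting, 7 per sequence and no carry-over:

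| ρ | Type I error, pre-test 5% / 10% | Power for 15 points: crossover test alone | Power, two-stage, pre-test 5% / 10% |
|---|---|---|---|
| 0 | 6.2% / 6.8% | 68.1% | 67.2% / 66.2% |
| 0.3 | 6.8% / 7.6% | 82.7% | 81.2% / 79.3% |
| 0.5 | 7.3% / 8.1% | 92.9% | 90.8% / 88.6% |
| 0.7 | 7.9% / 8.6% | 99.3% | 96.9% / 94.4% |
| 0.8 | 8.1% / 8.9% | >99.9% | 97.5% / 94.9% |

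The crossover test alone stays at 5.0% throughout. The composition of the error at ρ = 0.5 with the pre-test at 5% shows where the excess arises. The positive branch is entered in 5.11% of null trials, and the period-1 test then rejects in 50.3% of them: 0.0511 × 0.503 = 2.6%. The other 94.9% reject at about 5.0%: 4.8%. The sum is 7.3% after rounding. With the pre-test at 10%, the rejection rate inside the branch is 35%.

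**5. Keeping the interaction in the model.** A mixed model was fitted to one generated data set of 14 patients:

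| Model | Treatment coefficient | SE |
|---|---|---|
| Treatment + period | −15.38 | 5.63 |
| With interaction, reference coding | −11.94 | 8.66 |
| With interaction, centred coding | −15.38 | 5.63 |

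The reference-coded coefficient equals the period-1 between-patient difference in that data set (−11.94). Centred coding, or equivalently a contrast averaged over periods, returns the estimate and SE of the model without the interaction.

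**The case against.** The strongest reply is that the article never says what either branch does. Analysing period 1 alone is a familiar procedure, but it is not written anywhere in the document. An apparent interaction might only lead to effects being described by period, with the treatment test unchanged. In that case there is no inflation at all. The threshold and the content of the branches may also stand in an analysis plan that is not shown. This reply stands: the inflation is conditional, and a reader who infers that the trial's type I error simply is not 5% goes further than the text allows.

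A reader might also infer that power collapses to 41%. That figure belongs to the period-1 contrast taken by itself. Without carry-over, the assumed rule reaches that contrast in only about 5% or 10% of trials, so overall power stays at about 91% or 89% at ρ = 0.5. The 50% and 35% false-positive rates likewise apply only inside that branch.

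Nor does listing the interaction by itself forfeit the within-patient comparison. That happens only if the model is reference-coded and the raw treatment coefficient is reported as the effect. Coding is ordinary analysis-plan detail.

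Finally, the no-carry-over argument in the Discussion does not make a check on it purposeless. The check is merely weak with 14 patients.

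The reply does not remove the two statements about the same term that cannot both be true, or the printed rule that the data will choose the analysis. The section's opening emphasis on treatment and period, together with its closing line, suggests that treatment + period was the intended primary model. If so, the correction is easy, but it still has to be made.

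**Conclusion.** The point holds in a limited form. The statistical methods section contradicts itself on whether the interaction is in the primary model, and it announces a data-dependent choice of analysis. The primary treatment effect is therefore not fixed, and the secondary outcomes inherit the problem. This conclusion rests on the text alone.

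The size of the consequence rests on assumptions. If an apparent interaction leads to period 1 alone, with a pre-test at 5% or 10%, type I error is about 7–8% at ρ = 0.5 and about 6–9% over ρ from 0 to 0.8. Overall power at ρ = 0.5 falls from 93% to about 91% or 89%. If the branch only adds description, the error stays at 5%. The single-period coefficient arises only under reference coding without averaging over periods.

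**What to change.** - Delete the sentence that makes the analyses depend on the interaction.
- State the primary model as treatment and period (fixed) plus patient (random), and name its treatment effect as the single primary result whatever the interaction shows.
- Remove the interaction from the primary model's list of explanatory variables. Keep it only as the sensitivity analysis already planned, reported descriptively, for example as effects by period. Note that with complete data the treatment effect averaged over periods equals the primary estimate, so that average adds no information as a sensitivity result.
- Apply the same wording to the secondary outcomes.

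Under the sizing assumptions (SD of within-patient differences 15, 14 patients) this gives a type I error of 5.0% and power of 92.9%. The cost is a change of wording before database lock, with no added patients, visits or data. The downside is that absence of carry-over remains an assumption, as the Discussion already argues. A 7-against-7 pre-test would have given little protection against it in any case.
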